India started COVID-19 vaccination with BBV152 vaccine (Covaxin; Bharat Biotech) and ChAdOx1 nCoV-19 vaccine (COVID-19 Vaccine AstraZeneca) since January 16, 2021 under Emergency Use Authorization for the health care workers. The vaccination strategy was expanded for frontline workers in February 1, 2021 for frontline workers. In Phase 2 individuals above 60 years old and above 45 years old with specified comorbidities

became eligible for vaccination from March 1, 2021 followed by Phase 3 for all above 45 years of age from April 1, 2021. And finally Phase 4 for all above 18 years of age began on May 1, 2021 (6). Around 44 million individuals have received two doses while 160 million have received at least one dose of vaccine as on May 29, 2021 (7).

Population-based sero-epidemiological studies measure the presence of antibodies against SARS-CoV-2 (natural and vaccine induced) in different age groups. Repeated cross sectional serosurveys conducted in the same geographical location provide estimates to monitor trends over a period of and provide information valuable for the public health decision makers to design and revise containment strategies (8). The earlier serosurveys were conducted among individuals aged 10 years and above and seroprevalence among children below 10 years is still unknown. SARS-CoV-2 poses a high occupational risk to healthcare workers who are at the forefront of managing COVID-19 cases in hospital settings. The third serosurvey indicated seroprevalence around 25% among the HCWs. Also, the HCWs were prioritised for COVID-19 vaccination in the first phase of vaccine rollout in India owing to higher risk of exposure to infected persons.

In this context, it is proposed to conduct fourth round of serosurveillance to determine the prevalence of SARS-CoV-2 antibodies in the community and health care workers as per change in epidemiology and public health response to the epidemic in the country.

The objectives of the fourth survey are:

1. Estimate the prevalence of SARS-COV-2 antibodies among (a) children aged 6-17 y and (b) adults in the general population, at the national level
2. Estimate the prevalence of SARS-COV-2 antibodies among healthcare workers at the national level

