### **Sample size**

#### A] General population

We plan to enrol 28,000 individuals (19,600 individuals in the age group  $\geq 18$  years, 5600 children in the age group of 10-17 years and 2,800 children in the age group of 6-9 years) across the country by allocating a minimum of 400 individuals to each of the 70 districts that were included in the earlier survey. We have divided the overall sample size of 28,000 in the above-mentioned age groups as per age structure of the population (Census 2011).

The sample size assuming a seroprevalence of 30%, with 10% relative precision, for 95% CI and design effect of 2 would be 1792 for children in the 6-9 age group. The required sample size is sufficient to estimate prevalence for each age group. However, in order to have a sufficiently large sample for a national level survey, we will keep the same overall sample size for the fourth serosurvey.

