### **Sampling method**

#### A] General population

We will select 10 clusters (villages in rural areas and wards in urban areas) for each of the district by Probability proportional to size sampling. In each of the selected village/ward, we will select four random locations. In each location, the survey team will choose a random start household and visit consecutive households until 7 individuals from age-group  $\geq 18$  years, 2 children in the age group of 10-17 years and 1 child in the

age group of 6-9 years are enrolled. All household members, 6 years and older, will be included. Within each cluster, 40 individuals (28 individuals from  $\geq 18$  years, 8 children in the age group of 10-17 years and 4 children in the age group of 6-9 years) will be included for the survey. Individuals with history of laboratory confirmed SARS-CoV-2 infection by RT-PCR and/or rapid antigen test will not be excluded. SARS-CoV-2 cases in home isolation will not be included in the survey.

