### **Analysis plan**

#### **A] General population**

We will calculate the frequency of characteristics of survey participants. The reported occupations will be categorised into high and low risk considering the potential risk of exposure to known or unknown COVID-19 case.

We will estimate the seroprevalence of SARS-CoV-2 infection along with 95% confidence intervals using appropriate sampling weights and considering the cluster sampling used for the survey. We will define an antibody positive case as an individual whose sera tested positive on either of the two assays. Hence the sero-prevalence estimated will be based on presence of either N antibodies or S1-RBD antibodies. The final prevalence estimates will be calculated after adjusting for the IgG test performance characteristics of both assays.

We will use the survey data analysis module in STATA software (StataCorp LLC, Texas, USA).

We will separately estimate the seroprevalence of infections only among the adults. In order to maintain comparability with the previous surveys, we will randomly select one adult survey participant per household from the survey database.

We will estimate proportion of individuals with COVID-19 vaccination along with 95% CI. We will also estimate the seroprevalence with 95% CI for SARS-CoV-2 infection by age, sex, locality, occupation, symptom status, contact history, RT-PCR testing and confirmation status.

We will estimate the infection-to-case ratio as the number of individuals with SARS-CoV-2 infection (as per IgG detection) compared to the number of RT-PCR reported cases of COVID-19. We will apply the seroprevalence to the total population above 10 years projected for the year 2020 using 2011 census data to estimate the number of infections in the country. The published literature indicates that the IgG antibodies against SARS-CoV-2 infection start appearing by the end of first week, and most cases are IgG positive by the end of the second week (10). We will consider the number of reported COVID-19 cases 15 days and one week before the initiation of serosurvey to estimate the plausible range of the number of infections. We will estimate the range of the infection fatality ratio (IFR) assuming a three-week lag time from infection to death (11,12)

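### The only adult-specific estimate uses one random adult per household, which costs precision on objective 1(b), is not needed for valid errors, and leaves the household weight unstated

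*Combined protocol and SAP*

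**What the plan says.** The objectives at the end of the protocol's background ask for the prevalence among "b) adults in the general population, at the national level". The Sample size section (general population) plans "19,600 individuals in the age group" of 18 years and over, out of 28,000. Under Sampling method, teams at each of four locations per cluster "visit consecutive households until 7 individuals from age-group" 18 and over have been enrolled, alongside quotas for children. The same paragraph states: "All household members, 6 years and older, will be included". Several adults from one household will therefore often be in the sample. Laboratory procedures has all sera tested on both assays.

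The Analysis plan (general population) first describes an overall estimate using suitable but unspecified sampling weights and allowing for the cluster design. A later short paragraph turns to adults: "We will separately estimate the seroprevalence of infections only among the adults". It continues: "In order to maintain comparability with the previous surveys", "we will randomly select one adult survey participant per household from the survey database". The plan does not say whether the weights for this subsample include the number of adults in the household, and it names no adult estimate on the full set of enrolled adults.

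**The concern.** Adult prevalence is half of the first objective, yet the only estimate named specifically for adults leaves out part of the adult data already collected and tested. Two things follow.

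- **Precision.** Keeping one adult per household is not required for a valid confidence interval. Variance computed between villages or wards picks up all correlation below that level, including correlation within households. The thinning therefore gives up information without making the error estimate more valid.
- **Representation.** An adult in a household with k enrolled adults is kept with probability 1/k. Unless the weight is multiplied by k, adults from larger households count for less than their share. The plan is silent on this, so two analysts following it could produce different national adult figures.

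**Working it through.** **Planned figures.** Adults: 70 districts × 10 clusters × 4 locations × 7 adults = 19,600, as planned. The stated sample size for ages 6-9 also reproduces: 2 × 1.96² × 0.3 × 0.7 / 0.03² = 1,792.7, against 1,792 in the plan.

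**Share of adults left out.** Let m be the mean number of enrolled adults per household. The documents do not give m; I assume 1.5 to 3. The share left out is 1 − 1/m:

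| m (assumed) | Adults kept | Left out |
|---|---|---|
| 1.5 | 13,067 | 33% |
| 2 | 9,800 | 50% |
| 2.5 | 7,840 | 60% |
| 3 | 6,533 | 67% |

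Stopping at 7 adults per location truncates the last household and lowers these shares. With equal household sizes, m = 2 needs 4 households per location (1 − 4/7 = 43% left out) and m = 3 needs 3 (1 − 3/7 = 57%). A simulation with the 7-adult stop and an assumed household mix averaging 2.87 adults left out 59% when all adults were available, and 52%, 44% and 32% at 80%, 60% and 40% availability. Roughly one-third to two-thirds is a fair range.

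**Standard error.** Split the variance of one response into a cluster share c, a household share h and a remainder 1 − c − h. With 700 clusters and H = 19,600/m households, in units of p(1 − p):

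- all adults: V_all = c/700 + h/H + (1 − c − h)/19,600
- one per household: V_one = c/700 + (1 − c)/H

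The assumed ranges are c = 0.02 to 0.10 and h = 0.1 to 0.3. The two ends:

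- m = 1.5, c = 0.10, h = 0.3: V_all = 196.4 × 10⁻⁶ and V_one = 211.7 × 10⁻⁶. SE ratio √(211.7/196.4) = 1.04.
- m = 3, c = 0.02, h = 0.1: V_all = 88.8 × 10⁻⁶ and V_one = 178.6 × 10⁻⁶. SE ratio √(178.6/88.8) = 1.42.

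The standard error therefore rises by 4% to 42%. The formula ignores unequal weights.

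**What that means in points.** At the plan's 30% prevalence, the half-width is 1.96 × √(0.21 × V). In the 42% case it goes from 0.85 to 1.20 points. In the 4% case it goes from 1.26 to 1.31. The widest one-per-household half-width over the whole grid (m = 3, c = 0.10) is 1.5 points. That is 1.5/30 = 5% relative, inside the 10% criterion.

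**Representation.** As an illustration, assume 10/40/20/18/7/5% of households have 1 to 6 adults (mean 2.87) and ignore the 7-adult stop. Households with four or more adults then hold (4 × 0.18 + 5 × 0.07 + 6 × 0.05)/2.87 = 1.37/2.87 = 48% of adults, but supply 18 + 7 + 5 = 30% of an unweighted one-per-household subsample. If prevalence is the same at every household size, this shift causes no bias. The documents give no relation between the two.

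**The case against.** The strongest defence is the stated purpose. The rule stands in a separate paragraph and is justified by comparability with previous rounds, so it can be read as a trend analysis. Seroprevalence by age is also planned, and could supply an adult figure from everyone enrolled. This has weight, but the analysis set for the age breakdown is not stated, and the adult paragraph does not call itself secondary. Comparability is a good reason to keep the subsample estimate, but not to make it the only adult-specific estimate named.

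Three further points stand and limit the concern:

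- **The sera are not thrown away.** The one-per-household rule is not applied to the overall estimate, so a reader who infers that the blood was collected for nothing goes too far.
- **Precision remains ample.** At m = 3 about 6,500 adults are left, against the 1,792 computed for ages 6-9 and a sample size the plan calls sufficient for each age group.
- **Bias is not shown.** A reader might infer that the adult estimate is biased towards small households. The plan's general promise of suitable sampling weights could include the number of adults, and even without it there is no bias unless prevalence changes with household size. Any figure in points would rest on an invented household mix and an invented gradient.

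Reliance on a single random draw is not a separate defect: sampling error from the draw is part of the subsample's standard error.

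**Conclusion.** The point holds as a free improvement. As written, the adult-specific estimate for objective 1(b) leaves out roughly one-third to two-thirds of enrolled adults and has a standard error about 4% to 42% larger than necessary. This rests on 1.5 to 3 enrolled adults per household, a cluster ICC of 0.02 to 0.10 and a household component of 0.1 to 0.3, none of which is in the documents. The objective is not endangered, because the 10% relative precision criterion is met throughout that range.

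The household weight is an omission in the specification, not a demonstrated bias. It is tempting to state that half to two-thirds of adults are certainly lost, or to give a bias in percentage points; the documents support neither. The first needs a household size that they do not give, and the second needs a prevalence gradient as well.

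**What to change.** In the Analysis plan (general population):

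1. Base the objective 1(b) adult estimate on all enrolled adults, with the sampling weights and with variance computed at village/ward level.
2. Keep the one-adult-per-household estimate as a labelled secondary trend analysis. Name the earlier rounds it is compared with and weight it as those rounds were weighted; the documents do not say which rounds took one adult per household or how they were weighted.
3. State whether those weights include the number of adults per household.

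Averaging the subsample over many random draws is not recommended. Combined with a weight of k it converges on the all-adult estimate, leaving no separate trend analysis.

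The cost is analysis-plan wording and one extra estimate. No new data or samples are needed.

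### National infections, the infection-to-case ratio and the IFR count vaccine-induced antibodies as infections; the antibody-prevalence objectives are not affected

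*Combined protocol and SAP*

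**What the plan says.** The relevant text is in the Analysis plan, A] General population.

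- Positivity: "We will define an antibody positive case as an individual whose sera tested positive on either of the two assays". The next sentence confirms the basis: "Hence the sero-prevalence estimated will be based on presence of either N antibodies or S1-RBD antibodies". No separate definition of a past infection is given.
- Infections: the result is labelled a prevalence of infection and scaled up: "We will apply the seroprevalence to the total population above 10 years projected for the year 2020 using 2011 census data".
- Ratio: "We will estimate the infection-to-case ratio as the number of individuals with SARS-CoV-2 infection (as per IgG detection", set against reported RT-PCR cases.
- IFR: "We will estimate the range of the infection fatality ratio (IFR) assuming a three-week lag time from infection to death".
- Adjustments: sampling weights, clustering and assay performance. None concerns vaccination.
- Strata: "by age, sex, locality, occupation, symptom status, contact history, RT-PCR testing and confirmation status". Vaccination status is not listed. Vaccination details are recorded under Study procedures, but their only stated use is a coverage proportion.

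The background text says that such surveys "measure the presence of antibodies against SARS-CoV-2 (natural and vaccine induced) in different age groups" and that "160 million have received at least one dose of vaccine as on May 29, 2021". Both objectives are worded as antibody prevalence.

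**The concern.** The either-assay rule answers the question of who has antibodies. The ratio and the IFR need a different quantity, who has been infected. The plan uses the first as the second, although its own background separates the two sources of antibody.

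This problem is new in the fourth round. The third survey ended on 6 January 2021 and vaccination began on 16 January 2021, so reading IgG as infection was not disturbed by the roll-out before.

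At stake are the national infection count, the ratio and the IFR, together with the claim under Expected benefits that the survey will measure what the second wave did to transmission. The roll-out phases described were defined by age, occupation and comorbidity, and none covers children. Estimates labelled as infection by age and occupation will therefore partly reflect vaccine eligibility.

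**Working it through.** **The plan's own figures.** The documents state no infection-to-case ratio or IFR, so there is none to reproduce. The one computed design figure does reproduce: 2 × 1.96² × 0.30 × 0.70 / (0.10 × 0.30)² = 1792.7, against 1792 stated. It is used here only for its 30% and its design effect of 2.

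**Inputs from the documents.** 160 million with at least one dose; about 25 million reported cases; assay specificities of 99.90% and 99.6%; planning prevalence of 30%.

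**Assumed inputs, not in the documents.**
- Share vaccinated, v: 13% (160 million over about 1.2 billion people is 13.3%), or 25% to allow for growth by June–July.
- Share of uninfected vaccinees who test positive, s: 50% or 80%.
- Share truly infected, p: 30% or 60%.
- Infection independent of vaccination; assay error ignored.

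**Formula.** Either-assay prevalence = p + (1 − p) × v × s. Infections and the ratio are multiplied by (either-assay prevalence)/p, and the IFR by the inverse.

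| p | v | s | Either-assay prevalence | Infections overstated | IFR lowered |
|---|---|---|---|---|---|
| 30% | 13% | 50% | 34.6% | 15% | 13% |
| 30% | 13% | 80% | 37.3% | 24% | 20% |
| 30% | 25% | 50% | 38.8% | 29% | 23% |
| 30% | 25% | 80% | 44.0% | 47% | 32% |
| 60% | 13% | 50% | 62.6% | 4% | 4% |
| 60% | 13% | 80% | 64.2% | 7% | 6% |
| 60% | 25% | 50% | 65.0% | 8% | 8% |
| 60% | 25% | 80% | 68.0% | 13% | 12% |

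First row in full: 0.30 + 0.70 × 0.13 × 0.50 = 0.3455; 0.3455/0.30 = 1.15; 0.30/0.3455 = 0.87.

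**In persons, from the 29 May totals.** This needs no population figure. At p = 30%, 160 million × 0.70 × 0.5 to 0.8 = 56 to 90 million extra infections, or 2.2 to 3.6 per reported case on 25 million. At p = 60%, 160 million × 0.40 × 0.5 to 0.8 = 32 to 51 million, or 1.3 to 2.0 per case. The plan will use case counts 15 days and one week before the survey starts, so these show scale only.

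**Can the assay adjustment remove it?** No. Vaccine-induced IgG is a genuine antibody, not an assay error. By the quoted specificities, false positives on either assay are at most 0.1% + 0.4% = 0.5% of antibody-negative people, so the correction moves the estimate by less than 0.5 percentage points. The excess in the table is 2.6 to 14 points.

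**Against sampling error.** With 28,000 participants and a design effect of 2, the 95% half-width at 30% is 1.96 × √(2 × 0.30 × 0.70 / 28,000) = 0.76 points. At v = 13% the excess is 4.6 to 7.3 points, about 6 to 10 half-widths. In the mildest row (p = 60%) it is 2.6 points against a half-width of 0.81, about 3 half-widths.

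**Dependence.** If 45% of vaccinees were infected with 30% overall, the 15–24% at v = 13% becomes 0.13 × 0.55 × (0.5 to 0.8) / 0.30 = 12–19%. Correlation in the other direction would raise it.

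**The case against.** Several points on the other side stand.

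- The objectives ask for antibody prevalence, which the either-assay rule serves. The health care worker analysis is also worded as antibodies. A reader might infer that the survey's main results are wrong; the documents do not support that. The fault lies in derived outputs and in the infection label.
- A reader might infer that the final ratio is too high and the final IFR too low. Only this component has a known direction. The plan scales to the population above 10 years and states no matching age limit on reported cases, which pushes the ratio the other way. Death reporting and antibody waning are not quantified.
- No single percentage can be read from the documents. Population, seroconversion and later coverage are assumed. The 30% is a sample-size input, shown for ages 6–9, not an estimate of infection after the second wave. It lies near the third survey's 24.1%, which preceded that wave, and a low p enlarges the bias.
- The age and occupation results are descriptive. No adult-versus-child or older-versus-younger comparison is specified, so this is a labelling problem rather than a confounded test.
- A reader might think that the N assay alone solves the problem. The background names two vaccines but not the antibodies they induce, so this cannot be established from the documents.
- Restricting to undosed participants can bring its own selection. Standardising by age, sex and urban/rural alone would leave out occupation and comorbidity, which governed eligibility.

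None of these supplies a step that removes vaccine-induced positives from the infection count.

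**Conclusion.** The concern holds for the infection count, the infection-to-case ratio and the IFR, which are wrong as written. If any uninfected vaccinee tests positive, this component raises the first two and lowers the third. Under the stated assumptions the overstatement of infections is about 15–47% at 30% truly infected and about 4–13% at 60%, with the IFR lowered by about 13–32% and 4–12%. These are illustrations over assumed coverage, seroconversion and independence, not predictions. They make no claim about the net error in either output.

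**What to change.** 1. Call the either-assay result antibody prevalence throughout, and keep it for the objectives.
2. Add vaccination status (0, 1 or 2 doses) to the listed strata.
3. Base the infection count, the infection-to-case ratio and the IFR on seroprevalence among participants with no vaccine dose. Standardise it to the target population by age, sex, urban/rural and occupational risk, and by comorbidity where the recorded clinical history allows. The weighted distribution of all participants, dosed and undosed, can supply the standard.
4. Report the either-assay version of these outputs alongside, described as an upper bound with respect to vaccine-induced positives only.
5. Optionally, use N-assay positivity in vaccinees as a sensitivity analysis, if the sponsor confirms which antibodies each vaccine induces.

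The cost is analysis-plan wording and programming; vaccination details are already collected, and sampling and testing do not change. The plan should state two downsides. Fewer participants contribute to the infection estimate, so its interval widens, most in groups with high coverage. The estimate also assumes similar infection risk in vaccinated and unvaccinated people within strata.

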## **Population-based serosurvey to estimate prevalence of SARS-CoV-2 antibodies in India: Fourth survey, June - July 2021**

India is witnessing a second wave of SARS-CoV-2 infections from February 2021, spread across majority of states of India (1). As of May 29, 2021, India had reported around 25 million cases and more than 3,00,000 deaths (2). The first round of national serosurveillance was conducted from May 11, 2020, to June 4, 2020, among adults in randomly-sampled 700 clusters selected from 70 districts of 21 Indian states. The population-weighted seroprevalence after adjusting for test performance was 0.73% (95% CI: 0.34-1.13). The second round of nationwide serosurvey was conducted between 17 August and 22 September 2020 among individuals aged 10 years and above in the same clusters from 70 districts of 21 states (3). The findings indicated an overall seroprevalence of around 7%, with a ten-fold rise in adult prevalence between May and August 2020. It also indicated a substantial transmission in rural areas with the seroprevalence continuing to be higher in urban slum and non-slum areas (4).

ICMR conducted the third population-based serosurvey among individuals aged 10 years and above and health care workers between Dec 18, 2020 and Jan 6, 2021 in the same 700 villages or wards from 70 districts in 21 states selected for the first and second serosurveys. In the third serosurvey, prevalence was estimated based on the presence of both IgG antibodies against SARS-CoV-2 S1 protein of the receptor binding domain (S1-RBD) and nucleocapsid (N) protein of SARS-CoV-2 while in second serosurvey prevalence was based on IgG antibodies nucleocapsid (N) protein of SARS-CoV-2. The weighted and assay characteristic adjusted seroprevalence among general population was 24.1 (95%CI: 23.0% to 25.3%) The survey indicated that three fourth of the population were still susceptible and a higher sero-prevalence of SARS-CoV-2 infection in urban areas compared to the rural areas (5). Apart from the nationwide serosurveys, several cities and states conducted serosurveys. Metropolitan cities like Delhi, Mumbai, Pune, Chennai, Ahmedabad, Hyderabad have reported seroprevalence ranging between 17.6% and 56% at different timepoints (5).

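### The infection-to-case ratio names only RT-PCR cases as its denominator; applied literally, this leaves out antigen-only cases and raises the ratio

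*Combined protocol and SAP*

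**What the plan says.** Four places in the combined protocol and SAP bear on this.

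- **Analysis plan, A] General population, definition of the ratio.** Infections identified by IgG are "compared to the number of RT-PCR reported cases of COVID-19".
- **Same paragraph, number of infections.** "We will apply the seroprevalence to the total population above 10 years projected for the year 2020 using 2011 census data". The infection count is therefore a prevalence multiplied by a population, with no reference to test type.
- **Same paragraph, range step.** "We will consider the number of reported COVID-19 cases 15 days and one week before the initiation of serosurvey". No test is named here.
- **Sampling method, A] General population.** "Individuals with history of laboratory confirmed SARS-CoV-2 infection by RT-PCR and/or rapid antigen test will not be excluded". The context is who may take part in the survey, but the sentence treats either test as laboratory confirmation.

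The introduction gives a national total, again without a test type: "As of May 29, 2021, India had reported around 25 million cases and more than 3,00,000 deaths". No section names the surveillance source for the denominator, says whether that source can be split by test, or gives a reason for restricting it to RT-PCR. The list of subgroup analyses also ends with an item that joins RT-PCR testing and confirmation status and does not mention antigen tests.

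**The concern.** An infection-to-case ratio is normally read as the number of infections per case that surveillance detected. For that reading, numerator and denominator must cover the same infections: everyone infected above the line, everyone detected below it. Here the numerator includes a person confirmed only by rapid antigen test, while the stated denominator does not. Such a person was detected but is counted as missed. The bias can go only one way, towards a larger ratio and apparently poorer case detection.

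There is also a reproducibility problem. One analyst could follow the defining sentence and another the range step. They would use different denominators and report different national ratios, each able to point to the plan.

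**Working it through.** **Is there a stated figure to reproduce?** Not for this ratio: the plan gives neither an expected value nor a case count by test. The check is therefore algebraic, with an illustration under stated assumptions.

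**Step 1: the factor.** Let I be the estimated number of infections, C all laboratory-confirmed reported cases, and r the share of C confirmed by rapid antigen test only.

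- Ratio with all cases: I / C
- Ratio with RT-PCR cases only: I / [C(1 - r)]
- Second divided by first: 1 / (1 - r)

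I cancels, so the factor does not depend on the seroprevalence or on the population projection.

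**Step 2: which share matters.** Because the sampling section allows confirmation by either test or both, some people will be positive on both. They remain in an RT-PCR count. So r is the antigen-*only* share. Putting the share with any positive antigen test into the formula would give an upper bound.

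**Step 3: size over an assumed range.** The documents do not give r.

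| Assumed r | 1/(1 - r) |
|---|---|
| 0% | 1.00 |
| 10% | 1.11 |
| 20% | 1.25 |
| 30% | 1.43 |
| 50% | 2.00 |

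**Step 4: illustration on the ratio scale.** Inputs: 30% seroprevalence (the planning value in the Sample size section), 25 million reported cases (introduction, taken here as covering all tests), and 1.1 billion people above 10 years (my assumption; the plan does not state the projected population).

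- Infections: 0.30 × 1,100 million = 330 million
- All cases: 330 / 25 = 13.2
- r = 10%: 330 / 22.5 = 14.7
- r = 30%: 330 / 17.5 = 18.9
- r = 50%: 330 / 12.5 = 26.4

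With 1.0 or 1.2 billion people, the all-case ratio is 300 / 25 = 12.0 or 360 / 25 = 14.4. These values show scale only and do not predict the survey's result.

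**Step 5: what is not touched.** Seroprevalence uses no case count. The infection fatality ratio sets deaths against infections, and the infection count comes from seroprevalence and population. Neither changes with the choice of case denominator.

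**The case against.** The strongest reply is that RT-PCR is loose wording. The only national total in the documents carries no test type. If a total of that kind is used, the factor is 1.00 and there is no bias. This stands as a condition: the inflation arises only if the restriction is applied literally and r is above zero. It does not rescue the text, because the defining sentence would then describe something other than what is done.

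Several stronger readings are tempting, but the documents do not support them.

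- *A reader might infer that the two sentences contradict each other.* They belong to one paragraph on one calculation, and the later one is about timing, so its wording may be shorthand for the RT-PCR cases already named. This is an unresolved ambiguity. On the shorthand reading, however, the restriction governs both steps and the bias remains.
- *A reader might infer that the sampling section sets the national case definition.* It does not; it concerns participation in the survey. It shows only that the protocol recognises antigen confirmation.
- *A reader might infer that antigen-confirmed participants will be grouped with the unconfirmed in the subgroup analysis.* The subgroup item can equally mean two things: RT-PCR testing, and confirmation by any test. The Study procedures section collects COVID-19 testing details without limiting the type of test.
- *A reader might want to rank this effect above the choice between the 15-day and one-week case dates.* No case counts are given for those dates, so the comparison cannot be made.

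It is also fair to say that the ratio is a derived output outside the two stated objectives, and that correcting the denominator does not settle the numerator. Positivity on either assay, including S1-RBD, can reflect vaccination, and the introduction reports 160 million people with at least one dose. That is a separate matter.

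**Conclusion.** The point holds in a conditional form. The plan states a specific denominator, RT-PCR cases, that does not match a numerator indifferent to test type, and it gives no reason for the restriction. Applied literally, it multiplies the ratio by 1/(1-r): between 1.11 and 2.00 for an antigen-only share between 10% and 50%. That range is assumed, and the true share must come from the surveillance source. If all reported cases are used in practice, the result is unbiased and the wording is at fault. The plan needs correcting on either reading. The consequence is confined to the infection-to-case ratio and any statement about under-detection based on it, so this should be fixed but does not threaten the survey's main results.

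**What to change.** 1. In both the defining sentence and the range step, define the denominator as all laboratory-confirmed reported cases, by RT-PCR or rapid antigen test, and name the one national source from which they will be taken.
2. If an RT-PCR-only ratio is wanted, for example for continuity with earlier rounds, report it as a labelled secondary figure, and give the antigen-only share alongside it if the source can be split by test.
3. Word the subgroup as *RT-PCR or rapid antigen testing and confirmation status*, which removes the ambiguity there.

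The cost is a change of wording and the use of case totals covering both tests; no new survey procedure appears to be needed. The downside is that the ratio will be smaller than an RT-PCR-only version, and a note on comparability may be needed if earlier rounds used a different denominator.
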